## Abstract

**Background:**

Longitudinal observational studies have found an association between vision impairment and accelerated decline in cognition. However, no randomised trials have assessed the possible benefit of vision correction on cognitive change. We present the protocol for a three-year randomised controlled trial designed to assess the impact of spectacles for distance and/or near vision correction on cognitive change among community-dwelling elderly participants in India.

**Methods:**

Cognitive Level Enhancement through Vision Exams and Refraction (CLEVER) is a single-centre, open-label, parallel-group, individually-randomised trial. Participants (760 total, 380 in each arm) aged ≥ 60 years with correctable vision impairment at distance and/or near (presenting visual acuity < 6/18 in the better-seeing eye and improving to > = 6/18 with spectacles and/or presenting near vision worse than N6 at 40 cm and improving to N6 with spectacles), normal hearing (able to repeat at least three out of six words whispered from a 50 cm distance in the better ear) and normal cognition (Hindi Mini-mental Status Examination score > 18/31) will be enrolled. After a comprehensive eye examination, intervention group participants will receive distance, near, or bifocal spectacles, while controls will receive a prescription and spectacles at the end of the trial. The primary outcome will be the three-year change in Longitudinal Aging Study in India–Diagnostic Assessment of Dementia (LASI DAD) global cognitive factor score, with and without adjustment for baseline score, age, gender, education and other potential confounders.

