### Trial design

CLEVER is a single-centre, open-label, parallel-group, individually-randomised controlled trial, designed to test the impact of immediate versus delayed provision of free spectacles on rates of cognitive change among community-dwelling elderly persons.

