### Sample size

Based on the three-year, un-intervened decline in LASI-DAD (Longitudinal Aging Study in India–Diagnostic Assessment of Dementia) global cognitive score from a cross-sectional study of similarly aged persons in India [23, 24], with 90% power at *p* = 0.05 (two-tailed) using a two-sample t-test and estimated annual follow-up loss of 13% based on our other studies in this demographic group in the region, 760 participants across the two study groups are sufficient to detect a 29% effect size. Using a conservative estimate that 10% of screened persons will be eligible, an estimated 7600 will need to be screened to recruit 760 participants.

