### Randomisation, allocation and masking

The randomisation sequence will be generated by the trial statistician in the LVPEI CTU using an online randomisation tool (https://www.sealedenvelope.com). Stratified randomisation will be done based on gender (male/female), age (below and above median), education level (below and above median), and baseline HMSE (below and above median). Group allocation will be concealed from the trial coordinator and field team until a potential participant is determined eligible. Trial personnel will not be masked to participants’ treatment assignment due to practical difficulties in assessing the main trial outcome without study spectacles being worn. Masking of participants with use of zero-power spectacles among controls is not considered ethical in this setting.

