## Data management and analysis plan

Data will be collected on paper forms initially and then entered into an electronic database developed in Microsoft Access (Microsoft Corporation, Redmond, Washington, USA) at the data centre at Gullapalli Pratibha Rao International Centre for Advancement of Rural Eye care in Hyderabad, Telangana, India. Data will be securely stored in encrypted cloud-based institute servers. Personal data will be stored in a different database with access restricted to primary investigators. Data will be analysed at the end of the trial when all follow-up assessments are completed. All randomised participants will be assessed based on the intention-to-treat principle in the main analysis. Per-protocol analysis will also be conducted as secondary analysis, analysing participants according to treatment they actually received. No formal interim analysis will be done for the primary outcome measure.

Baseline characteristics and follow-up measurements will be summarised as mean and standard deviation, median and inter-quartile range, or numbers and frequencies (%) as appropriate, depending on the scale and distribution of measurements. Histograms or Q-Q plots will be used to assess the normality of all continuous variables.

Global cognitive factor scores for our study population will be calculated using the cognitive test data from the LASI-DAD battery. This calculation is similar to that performed in the ACHIEVE trial, which investigated the impact of hearing aids on cognitive decline [33]. In ACHIEVE, the global cognitive factor score was the primary outcome measure calculated using the ARIC (Atherosclerosis Risk in Communities) cognitive battery [33]. The between-group difference in three-year change in LASI-DAD global cognitive score (primary outcome) will be calculated. A linear mixed-model regression analysis with restricted maximum likelihood estimation will be used to assess between-group differences in change in LASI-DAD global cognitive score over time after adjusting for potential confounders (baseline cognitive score, age, sex, education, visual function, quality of life, depression, falls, social interaction, and physical activity).

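### The primary comparison is specified both unadjusted and adjusted with neither named as deciding, and the adjusted covariate list omits baseline HMSE, a stratification factor

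*Protocol article*

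**What the plan says.** The Abstract (Methods) gives one primary outcome, the three-year change in LASI-DAD global cognitive factor score, in two versions: "with and without adjustment for baseline score, age, gender, education and other potential confounders".

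Data management and analysis plan carries the same pair. First: "The between-group difference in three-year change in LASI-DAD global cognitive score (primary outcome) will be calculated". Next: "A linear mixed-model regression analysis with restricted maximum likelihood estimation will be used to assess between-group differences in change in LASI-DAD global cognitive score", adjusted for "baseline cognitive score, age, sex, education, visual function, quality of life, depression, falls, social interaction, and physical activity". Later in that section, a conventional two-sided 5% level is set for every result, with no ordering of the two analyses.

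Sample size bases the trial on an unadjusted comparison, "with 90% power at *p* = 0.05 (two-tailed) using a two-sample t-test".

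Randomisation, allocation and masking stratifies on gender, age, "education level (below and above median), and baseline HMSE (below and above median"). HMSE is the only one of the four stratification factors not named among the model's covariates.

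**The concern.** The trial has one primary question and two analyses of it, each read at 5%, with nothing to say which one counts. Two things follow.

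- If a significant result from either could be presented as success, the chance of a false positive would exceed 5%.
- If the two disagree, the published plan does not say what the trial has found. Disagreement is realistic. The sample-size section expects an "estimated annual follow-up loss of 13" per cent, so about a third of participants may have no 36-month score. A crude change score then rests on those who have one, while a mixed model can also use the 12- and 24-month visits.

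The trial is open-label with unmasked personnel, which makes a fixed deciding analysis more valuable than usual.

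Separately, analysis should reflect the way participants were randomised. The unadjusted comparison reflects none of the four stratification factors, and the adjusted one names three of them.

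**Working it through.** **1. Reproduce the plan's figure.** Inputs from Sample size: 90% power, two-sided 0.05, effect 29%, 13% loss per year, 760 in total. The 29% is read as 0.29 standard deviations; this is an assumption, since no SD is given.

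- Evaluable per arm: 2 × ((1.960 + 1.282) / 0.29)² = 249.9, so 250.
- Retained after three years: 0.87³ = 0.6585, so about 34% are lost.
- Randomised per arm: 250 / 0.6585 = 379.6, so 380, or 760 in total.

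The stated size is reproduced with a normal-approximation unadjusted test. No sample-size figure is in dispute.

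**2. What the article ranks.**

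| Place | What it gives | Declares it deciding? |
|---|---|---|
| Abstract, Methods | Both versions | No, equal standing |
| Data management and analysis plan, difference in change | Quantity with a primary-outcome label; no test or model named | No |
| Same section, mixed model | Method, estimation and ten covariates | No |
| Sample size | Two-sample t-test | No, sizing only |

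**3. Type I error if either result could be claimed.** Let R² be the share of outcome variance explained by the baseline covariates. The article gives no value, so 0.1 to 0.5 is assumed. If both analyses use the same outcome data, the two z-statistics under the null have correlation ρ = √(1 − R²). The error is P(|z₁| > 1.96 or |z₂| > 1.96) for a bivariate normal with that correlation. The ratio of unadjusted to adjusted standard error is 1/√(1 − R²).

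| Assumed R² | ρ | Either-result error | SE ratio |
|---|---|---|---|
| 0.1 | 0.949 | 6.5% | 1.05 |
| 0.2 | 0.894 | 7.1% | 1.12 |
| 0.3 | 0.837 | 7.6% | 1.20 |
| 0.5 | 0.707 | 8.3% | 1.41 |

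Independent tests would give 1 − 0.95² = 9.75%, an upper reference. The correlation formula is approximate because the mixed model may draw on visits that the crude change score does not use.

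**4. Power with the adjusted analysis deciding.** With 250 completers per arm and an effect of 0.29, power is Φ(0.29 × √125 / √(1 − R²) − 1.96). This gives 90.0% at R² = 0, 92.8% at 0.1, 95.2% at 0.2 and 97.2% at 0.3. Making the adjusted analysis decisive should not reduce power.

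**5. HMSE.** The stratification factors are gender, age, education and baseline HMSE; the covariate list has sex, age and education. Its baseline cognitive score most naturally means LASI-DAD, because in that paragraph the term is used for the LASI-DAD score, and the Abstract's baseline score follows the LASI-DAD outcome. Leaving a prognostic stratification factor out of the model tends to make standard errors too large, so the test is conservative.

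**The case against.** The strongest reply is that the plan already points one way. The primary-outcome label sits on the simple difference, and the sizing uses an unadjusted t-test of that quantity. This stands as a hint. But the label may only identify the variable, and the sentence names no test. It can equally be read as stating the quantity, with the next sentence giving the model for it. The Abstract treats both versions alike.

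A second reply is that ranking the analyses belongs in the statistical analysis plan. That would answer silence, but here the article positively states both versions.

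Four stronger readings are tempting, and the article does not support them:

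- **That the trial's type I error is 7% or 8%.** Nowhere does the article say that either result may be claimed. A general significance level is not a success rule, and reporting crude and adjusted estimates together is common.
- **That the estimand shifts between rate, three-year change and change over time.** Trial design does say "on rates of cognitive change among community-dwelling elderly persons", but as a general statement of purpose. The Abstract and the analysis plan both give three-year change, and no conflicting primary time point appears.
- **That omitting HMSE makes the test anti-conservative.** The effect runs the other way. Baseline LASI-DAD probably carries much of the same information, and a loose reading of baseline cognitive score might even include HMSE.
- **That the unadjusted analysis is underpowered.** The 760 were calculated for it at 90%.

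**Conclusion.** The point holds as a failure to name the deciding analysis, with a smaller mismatch between randomisation and model. The either-result error of about 6.5% to 8.3% depends on three assumptions: that either result could be claimed, that R² lies between 0.1 and 0.5, and that the correlation formula is close enough. It shows what is left open and is not an error rate the plan has adopted. The upper end is the least secure, because the crude outcome is already a change score and nothing in the article suggests that covariates explain half its variance.

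The certain part is that the article gives no rule for discordant results. Ignoring the stratification factors costs some precision in the unadjusted comparison; for HMSE alone, within the adjusted model, the loss is probably small.

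**What to change.** State one deciding analysis in the protocol and analysis plan, and match the Abstract and registry wording to it: the arm contrast at 36 months from the linear mixed model, adjusted for baseline LASI-DAD global score and all four stratification factors (sex, age, education and baseline HMSE). Label the unadjusted difference in three-year change as supportive, and say that it cannot by itself establish the primary result.

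The cost is wording only. HMSE is already collected at baseline, no new data are needed, and 760 stands. The one drawback is that the deciding analysis then differs from the t-test used for sizing; one sentence can note this and that power should not fall as a result.

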**Conclusion:**

CLEVER is designed to assess the effectiveness of spectacles as a low-cost intervention to prevent or delay cognitive decline.

**Trial registration:**

This trial is registered with ClinicalTrials.gov, number NCT05458323, February 15, 2023.

**Supplementary Information:**

The online version contains supplementary material available at 10.1186/s13063-025-08813-x.

## Background

Dementia is a major health problem, affecting more than 57.4 million people globally [1]. By 2050, dementia or cognitive impairment will affect an estimated 152 million persons worldwide [1]. The increase in prevalence is greater in low- and middle-income countries (LMICs) such as India, because of relatively faster ageing and increases in life expectancy [2, 3]. Dementia increases the risk of mortality and adversely affects individuals and families [4, 5]. The global cost of dementia care is predicted to exceed US$2 trillion by 2030 [6]. The annual per capita cost for dementia care in LMICs ranges from US$590 for mild cases to US$25,500 for severe ones [7]. A substantial economic burden for dementia care is also reported in India [8]. The Alzheimer’s and Related Disorders Society of India estimated the total societal cost of dementia to be US$3.4 billion in 2010, rising to 0.5% of India’s gross domestic product by 2050 [9].

Vision impairment (VI) is also an important public health issue, affecting a billion people worldwide [10]. It is more prevalent in individuals aged ≥ 60 years, affecting one out of every three older adults in India [11]. Vision impairment adversely affects quality of life and visual functioning [12]. Moreover, it results in substantial economic productivity loss [13]. Approximately 80% of VI can be addressed with low-cost interventions such as spectacles and/or cataract surgery [10]. A recent RCT among Indian tea pickers reported a 22% increase in productivity when spectacles were provided [14].

Both dementia and VI are more common in elderly persons [15]. In India, the population aged > = 60 years is estimated to rise from 8% in 2015 to 19.1% in 2050 [16, 17]. Significant increase in the prevalence of both dementia and VI are expected to accompany this demographic change [15]. Therefore, research to identify modifiable risk factors and low-cost interventions to slow cognitive decline and prevent mild cognitive impairment, a potential precursor to dementia, is particularly important for India.

Observational studies have consistently found a positive association between vision impairment and cognitive decline [18]. The hypothesized pathways through which VI may influence cognitive health include increases in social isolation, physical inactivity, depression and changes in brain structure and increased cognitive load [5]. However, only experimental interventional study designs, such as randomised controlled trials (RCTs), can establish a cause-and-effect relationship between vision care and cognitive change. No such trials have yet been done.

The Cognitive Level Enhancement through Vision Exams and Refraction (CLEVER) trial aims to assess the impact of spectacles for distance and/or near vision correction on cognitive change among community-dwelling elderly persons in Telangana, India, over three years. This trial also seeks to understand the cost-effectiveness and impact of near and distance spectacles on quality of life, falls, depression, social interaction, and physical activity among study participants. The current report describes the CLEVER trial protocol.

## Methods

### Ethics approval and governance

The Institutional Review Boards (IRBs) of the Hyderabad Eye Research Foundation, LV Prasad Eye Institute (LVPEI [LEC-BHR-P-09–746]), the National Institute of Mental Health and Neurosciences (NIMHANS) [NIMHANS/ 36th 1EC (BS & NS DIV.Y)/2022], and Queen’s University Belfast (QUB) [MHLS22-13] have approved the trial protocol. Written informed consent will be obtained from all participants before enrolment into the trial. CLEVER will be conducted following the tenets of the Declaration of Helsinki and regulations set forth by governing bodies including the Indian Council of Medical Research (ICMR). The Health Ministry’s Screening Committee clearance for projects involving international collaborations has also been obtained as mandated by the ICMR.

The following oversight committees are in place to ensure rigorous monitoring of trial progress, including safety, efficacy, protocol adherence, and compliance with ethical, regulatory, and sponsor requirements:

### Trial Management Group (TMG)

The TMG oversees day-to-day trial management. It meets fortnightly, and includes the Chief Investigator (CI), local lead, collaborators, representatives from the Northern Ireland Clinical Trials Unit (NICTU), LVPEI Clinical Trials Unit (LVPEI CTU), project manager, qualitative lead, and research students.

### Trial Steering Committee (TSC)

An independent TSC acts on behalf of the sponsor and meets at least annually to oversee conduct of the trial. The CLEVER TSC comprises six independent members with expertise in public health, psychiatry, geriatrics, and study designs, alongside a Patient and Public Engagement (PPI) representative to ensure participant-centred perspectives.

### Data Monitoring and Ethics Committee (DMEC)

This multidisciplinary committee includes trialists, statisticians, public health specialists, ophthalmologists, and one cognitive neurologist. The DMEC meets at least annually, with meeting frequency adjusted as necessary. It evaluates participant safety, intervention efficacy, and trial conduct, providing recommendations to the TSC, sponsor, funder, and CI regarding trial continuation or modification.

Additionally, the LVPEI CTU, in coordination with the NICTU, conducts regular trial monitoring and audits as delegated by the sponsor, Queen’s University Belfast. Onsite visits are conducted at least quarterly, with additional visits as required to ensure compliance with the approved protocol, Good Clinical Practices (GCP), and data accuracy.

Management of protocol amendments will comply with the requirements of the sponsor (Queen’s University Belfast and their Research Ethics Committee [REC]), local IRBs (L V Prasad Eye Institute and NIMHANS), and the Indian Council of Medical Research (ICMR). Substantial amendments will require prior approval from QUB REC and LVPEI IRB, except in cases of urgent safety measures. Amendments will also be reported to ICMR in an annual progress report. Approved protocol amendments will be distributed by the LVPEI CTU to the research team for inclusion in the Investigator Site File. The team will be trained on these amendments, with documentation completed before implementation.

CLEVER is registered with ClinicalTrials.gov and the Clinical Trials Registry-India, and both registries will be updated with approved amendments. Any protocol deviations will be documented using a deviation/breach form, including an explanation and corrective/preventive actions. Deviations will be reported to QUB REC, local IRBs, and ICMR as per their standard procedures and in the annual progress report.

### Trial design

CLEVER is a single-centre, open-label, parallel-group, individually-randomised controlled trial, designed to test the impact of immediate versus delayed provision of free spectacles on rates of cognitive change among community-dwelling elderly persons.

### Participants

Community-dwelling elderly persons aged ≥ 60 years at the time of enumeration will be recruited from subdistricts in Ranga Reddy district in the South Indian state of Telangana (Fig. 1), according to the following criteria:

**Fig. 1 Fig1:**
[figure not shown]
Map showing the study location (per-urban and rural location in Rangareddy district in Telangana state in India)

### Inclusion

Age ≥ 60 years at the time of enumeration.Resident in the household for > = 3 months and planning to reside in the local area for the trial duration.Distance vision impairment (VI, presenting visual acuity [VA] < 6/18 in the better-seeing eye and improving to > = 6/18 with spectacles) and/or near VI (presenting near vision < N6 at 40 cm and improving to > = N6 with spectacles).Independent mobility with or without the support of a walking stick.Hindi Mini-mental Status Examination (HMSE) questionnaire score > 18 (out of 31) [19].Willingness to participate, to be randomised to either study group, and to adhere to the protocol.

### Exclusion criteria

Serious medical illness likely to result in loss to follow-up. Those less severely affected by conditions such as hypertension and/or diabetes will be eligible [20].Failure on the whispered voice hearing screening test in the better ear (unable to repeat > = 3 out of 6 words whispered from behind the participant at a distance of 50 cm) [21, 22].

### Sample size

Based on the three-year, un-intervened decline in LASI-DAD (Longitudinal Aging Study in India–Diagnostic Assessment of Dementia) global cognitive score from a cross-sectional study of similarly aged persons in India [23, 24], with 90% power at *p* = 0.05 (two-tailed) using a two-sample t-test and estimated annual follow-up loss of 13% based on our other studies in this demographic group in the region, 760 participants across the two study groups are sufficient to detect a 29% effect size. Using a conservative estimate that 10% of screened persons will be eligible, an estimated 7600 will need to be screened to recruit 760 participants.

### Recruitment

Participants will be recruited through door-to-door household visits. Trained community eye health workers and social investigators will obtain written informed consent for preliminary screening after explaining study procedures. Each consenting participant will be assigned a unique identification number. The preliminary screening battery will include the following five components (Fig. 2):

**Fig. 2 Fig2:**
[figure not shown]
Study flowchart showing various stages of non-clinical and clinical assessment

1) vision screening to identify correctable VI at distance and/or near. Improvement in distance vision with pinhole is considered correctable VI (which will be confirmed with refraction in the clinical exam); 2) Ascertainment of independent mobility status, 3) Systemic medical history; [20] 4) hearing screening [21, 22]; and 5) screening for cognitive impairment using HMSE [19].

Social investigators will obtain written informed consent from all those eligible on the preliminary screening battery. Participants will be interviewed in their households and given appointments to visit the study clinic at the LVPEI centre (Shirin Etian & Tara Brown Eye Centre) in Kismatpur village, Ranga Reddy District, Telangana, for baseline clinical examination and cognitive testing [25, 26]. Those unable to visit the study site will be examined in temporary clinics set up in their vicinity.

